### Study design

2.1

This study is a randomized, double-blind, placebo-controlled superiority trial. It has been registered on the International Traditional Medicine Clinical Trial Registry Platform (registration number: ITMCTR2024000215) and approved by the Research Ethics Committee of Xiyuan Hospital, China Academy of Chinese Medical Sciences (approval number: 2024XLA060-2), confirming compliance with the Declaration of Helsinki, the 2020 Good Clinical Practice (GCP) guidelines for drug clinical trials, and the International Ethical Guidelines for Biomedical Research Involving Human Subjects (CIOMS). The decision to modify the protocol must be communicated by the Research Ethics Committee of Xiyuan Hospital, China Academy of Chinese Medical Sciences. The design of this study protocol follows the SPIRIT 2013 Statement (38, 39). The completed SPIRIT checklist is available in Supplementary File 3.

This study will be conducted at Xiyuan Hospital, China Academy of Chinese Medical Sciences, with a total of 60 participants to be recruited. After providing written informed consent, participants will be enrolled in the trial, which has a total treatment duration of 24 weeks, with follow-up visits scheduled at weeks 4, 12 and 24 of the intervention (Figure 1 and Table 1).

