### Randomization and allocation concealment

2.3

All patients who consent to participate in the study and meet the inclusion and exclusion criteria will be randomized in a 1:1 ratio to the control group or the experimental group. The statistical expert from the Clinical Pharmacology Research Institute of Xiyuan Hospital, China Academy of Chinese Medical Sciences, generated the sequence using SAS software (version 9.4) employing a stratified block randomization method, sequentially numbered from 1 to 60. The statistical expert will send the blind codes directly to the drug manufacturing department to label the investigational products. According to the clinical research protocol, the drug randomization code serves as the unique identifier for participants, and treatment allocation will remain undisclosed until the completion of data statistical analysis. Confidential information, including the selected block length, random seed parameters, the randomization sequence list, and emergency envelopes, is sealed in opaque envelopes and maintained by independent personnel from the Clinical Pharmacology Research Institute.

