(a)CT-FFR Assessment: CT-FFR was utilized as the core indicator of vascular function. The CT-FFR value was measured 2 cm distal to the stenotic lesion. For patients with multiple stenoses or multi-vessel involvement, the vessel with the most severe luminal stenosis and its most severe lesion were selected as the measurement point. The change before and after treatment was calculated (△CT-FFR = post-treatment − pre-treatment).(b)FAI Assessment: FAI was obtained to reflect the local inflammatory burden of the coronary artery. The FAI level was measured over a 10 mm length centered on the stenotic lesion. A higher value indicates more significant inflammatory infiltration of local adipose tissue. For patients with multiple stenoses, the most severe lesion was selected, and its change was dynamically tracked (△FAI = post-treatment − pre-treatment).(c)WSS Assessment: WSS reflects the frictional force exerted by blood flow on the vascular endothelium. WSS values were extracted at the most severe stenotic lesion. The change before and after intervention was tracked (△WSS = post-treatment − pre-treatment).(d)High-Risk Plaque Characterization: Based on the CAD-RADS™ 2.0 criteria (2), morphological instability features of the plaques were identified. A plaque must exhibit two or more of the following features to be classified as a high-risk plaque: ① Spotty calcification: Small, punctate calcified deposits observed within the plaque; ② Low-attenuation plaque: Non-calcified plaque areas with internal CT attenuation values below 30 HU; ③ Positive remodeling: The ratio of the outer vessel diameter at the plaque site to the average of the normal proximal and distal reference diameters is >1.1; ④ Napkin-ring sign: The simultaneous presence of two features on the cross-sectional image of a non-calcified plaque: a central low-attenuation core surrounded by a ring-like peripheral rim with higher CT attenuation.

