### Sample size

2.7

There are no studies using coronary artery hemodynamic parameters and FAI to evaluate the efficacy of traditional Chinese medicine in treating SCAD. This study is an exploratory trial and does not require sample size calculations (44). Sixty subjects will be recruited, with 30 participants allocated to each group, to investigate our research objectives.

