### Statistical analysis

2.9

According to the ITT analysis principle, the Full Analysis Set (FAS) is defined as the set of qualified cases that completed the study and analyzable drop-out cases, excluding excluded cases. The Per Protocol Set (PPS) is defined as the set of cases that comply with the trial protocol, have not concurrently used other drugs or treatments that may affect the trial results, have completed the full intervention and follow-up, and have completed the CRF as required. The Safe Set (SS) is defined as the set of cases that have received at least one dose of medication, possess baseline safety data, and have undergone at least one safety visit. Efficacy and safety will be evaluated based on the FAS, with the PPS used for sensitivity analysis.

Continuous variables will be described as mean ± standard deviation, categorical variables as frequency and percentage. Comparison of outcome measures between groups: continuous variables with a normal distribution will be analyzed using paired *t*-tests; those without a normal distribution will be analyzed using the Wilcoxon rank-sum test. Categorical variables will be compared using the *χ*^2^ test or Fisher's exact test. Subgroup analyses will be conducted based on whether patients have high-risk plaques (positive remodeling, low-attenuation plaque, spotty calcification, and napkin-ring sign) (2). Additionally, difficult-to-control and intergroup imbalanced confounding factors will be analyzed as covariates using analysis of covariance to eliminate their impact on efficacy evaluation. *P*-value <0.05 will be considered statistically significant. All statistical analyses will be performed using SPSS (version 25).

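### Section 2.9 names a paired t-test for comparing two independent randomised arms, on every continuous outcome judged normal, primaries included

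*Protocol article*

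**What the plan says.** Protocol article, section 2.9 (Statistical analysis), gives the rule for continuous outcomes in one sentence with two branches. For normal data: "Comparison of outcome measures between groups: continuous variables with a normal distribution will be analyzed using paired *t*-tests". For the rest: "those without a normal distribution will be analyzed using the Wilcoxon rank-sum test". No exception is made for the primary outcomes in section 2.6.1 (CT-FFR, WSS and FAI, measured at baseline and week 24), all of which are continuous.

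The design is parallel-group. Section 2.1: "This study is a randomized, double-blind, placebo-controlled superiority trial". Section 2.3: patients "will be randomized in a 1:1 ratio to the control group or the experimental group", from a sequence generated by "employing a stratified block randomization method, sequentially numbered from 1 to 60". Section 2.7: "Sixty subjects will be recruited, with 30 participants allocated to each group". No matched pairs and no crossover are described.

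The only other between-arm model for continuous outcomes is an ANCOVA in section 2.9. It is introduced as an additional analysis, for confounders that are imbalanced or hard to control. An independent-samples t-test is not named anywhere in the article.

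**The concern.** A paired t-test needs a link between the two values in each pair. Here that link exists within a patient over time, but not between a patient on SYF and a patient on placebo. The named test therefore does not fit its stated purpose. The two branches of the sentence also assume different data structures for the same comparison, so a normality check would switch the analysis from paired to unpaired.

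An analyst who follows the text literally has two options. One is to test pre against post within each arm, which leaves the placebo arm out of the inference: anything that moves both arms, such as background therapy or time, is credited to SYF. The other is to pair unrelated patients across arms in some order that the article does not define. In either case the headline p-value of a placebo-controlled trial would rest on a test that its design does not support.

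**Working it through.** The article states no power, effect size, SD or expected change, so there is no figure to reproduce. What follows illustrates the consequences of each reading.

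**Inputs.** From the article: n = 30 per arm (section 2.7) and significance at P < 0.05 (section 2.9). Assumed: two-sided testing, since sidedness is not stated; normal changes; and a common mean change c in both arms, in units of the SD of the change, from 0 to 0.8.

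**Reading 1: pre-post test within each arm, no SYF effect.** Each arm is a one-sample t-test on the change, with 29 df and noncentrality c√30. Let p be its probability of significance. The arms are independent, so P(SYF significant, placebo not) = p(1 − p).

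| c (SD of change) | p | p(1 − p) |
|---|---|---|
| 0 | 0.050 | 4.8% |
| 0.1 | 0.083 | 7.6% |
| 0.2 | 0.185 | 15% |
| 0.3 | 0.355 | 23% |
| 0.37 | 0.500 | 25% (maximum) |
| 0.5 | 0.754 | 19% |
| 0.6 | 0.888 | 9.9% |
| 0.7 | 0.959 | 3.9% |
| 0.8 | 0.989 | 1.1% |

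The 4.8% at c = 0 counts significance in either direction; in the favourable direction alone it is 2.4%. A valid two-sided 5% test would favour SYF falsely in 2.5% of trials.

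A simulation of 100,000 null trials at each of 0.2, 0.3, 0.5 and 0.8 SD gave 15%, 23%, 19% and 1.1% for the same event. The independent two-sample t-test on the same data stayed at 4.9% to 5.1% at every shift simulated, zero included.

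The fall at large shifts is no reassurance. At 0.8 SD both arms are nearly always significant, so the SYF arm taken alone would look positive in 99% of trials with no SYF effect.

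**Reading 2: pairing patients across arms.** With 30 pairs of unrelated patients, df fall from 58 to 29 and the critical t rises from 2.002 to 2.045. At a standardised difference of 0.735 the noncentrality is 0.735 × √15 = 2.847. Power is 79.9% for the independent test and 78.6% for the paired one, a loss of about 1.4 points before rounding. The difference detectable with 80% power moves from 0.74 to 0.75 SD.

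The larger defect is arbitrariness. In one simulated data set the independent test gave p = 0.008, while 5,000 random re-pairings gave p from 0.002 to 0.025 (central 95%). The paired test also cannot use all patients once the arms differ in evaluable numbers, and section 2.5.3 provides for dropouts and exclusions.

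**The case against.** The strongest reply is that this is a drafting slip. The clause says that it compares groups, and its companions (rank-sum, chi-square, Fisher) are all independent-samples tests. An ANCOVA is also planned. This is probably right about intent. It does not cure the text: the article does not leave the test open, it names one that does not fit, and the ANCOVA is additional and conditional.

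The trial also calls itself exploratory: "This study is an exploratory trial and does not require sample size calculations". That excuses the missing sample size calculation. It does not excuse an ill-fitting comparison in a trial that also calls itself a superiority trial and sets a significance threshold.

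Several stronger readings are tempting, and the article does not support them:

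- **A false-positive rate of 19% to 25%.** That is only the top of the curve, at common shifts of 0.3 to 0.5 SD. The article gives no shift, and it nowhere says that efficacy would be inferred from SYF being significant and placebo not. Stable concomitant dosing (section 2.5) and image readers blinded to time point (section 2.4) would limit some sources of common shift.
- **Regression to the mean flattering SYF because entry requires CT-FFR above 0.8.** That criterion (section 2.2.3) selects high readings. Regression would lower later CT-FFR, which counts against SYF, and the criterion does not concern FAI or WSS.
- **No valid test of the randomised contrast on any reading.** With equal arms, arbitrary cross-arm pairing keeps its type I error (5.0% in 200,000 simulated null trials). The failure to compare the arms belongs to the within-arm reading only.
- **A second error in section 2.6.4.** Its definition of change, "The change before and after treatment was calculated", is sound and suits either an independent t-test on change or an ANCOVA.

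**Conclusion.** The point holds as an error in the named method. As written, section 2.9 assigns a paired test to the comparison of two independent arms, for every continuous outcome judged normal, and CT-FFR, WSS and FAI are not exempt.

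The size depends on how the sentence is carried out. As within-arm tests, it does not compare SYF with placebo. The chance of a misleading pattern (SYF significant, placebo not) is then about 1% to 25% over assumed common shifts of 0 to 0.8 SD, provided that efficacy were inferred from that pattern. As cross-arm pairing, the loss of power is about 1.4 points; the real faults are a p-value that depends on an arbitrary order and the loss of patients when arm sizes differ.

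The wording error itself rests on no assumption. The percentages rest on 30 evaluable patients per arm, two-sided 5% testing, normal changes and the assumed shifts. It should be corrected before unblinding, because the sentence governs the primary outcomes and the correction is trivial.

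**What to change.** **Minimum.** In section 2.9, replace the paired t-test with the independent-samples t-test on change from baseline. Keep the rank-sum test, stated as applied to change, for non-normal outcomes. Label any paired test as a descriptive within-arm summary that carries no inference about SYF against placebo.

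**Preferred.** Make the main between-group analysis an ANCOVA of the follow-up value with treatment, baseline value and the randomisation strata as terms, reporting the adjusted difference with its 95% confidence interval. Apply it at week 24 for the CCTA outcomes and at each scheduled visit (weeks 4, 12 and 24) for TCMSS and SAQ. Retain a stated rule for non-normal outcomes.

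**Cost.** One sentence for the minimum and a short paragraph for the preferred version. No new data, visits or patients are needed. The change should be dated and made before the group codes in section 2.4 are opened, so that the test cannot appear to have been chosen after the results were seen.

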**Figure 1 F1:**
[figure not shown]
Flow chart of the study design. SCAD, stable coronary artery disease; SYG, Shenqi Yangxin Granule; NRP, Notoginseng Radix powder; GDMT, Guideline-Directed Medical Therapy; coronary artery hemodynamic parameters, include CT-FFR and WSS; TCMSS, traditional Chinese medicine syndrome scale.

**Table 1 T1:** Schedule for data collection of this study.

Items	Trial period				
	Enrollment		Post-randomization		Close-out
Timepoint	−7 d to 0d	0d	4w ± 3d	12w ± 3d	24w ± 3d
Enrollment					
Inclusion/exclusion criteria	×				
Informed consent	×				
Basic information	×				
Physical examination	×				
Medical History	×				
Randomization		×			
Intervention					
Treatment group (*n* = 30)		×	→	→	×
Control group (*n* = 30)		×	→	→	×
Assessments					
Coronary artery hemodynamic parameters		×			×
Fat attenuation index		×			×
Imaging features of high-risk plaques		×			×
TCMSS		×	×	×	×
Seattle angina questionnaire		×	×	×	×
Cardiology ultrasound		×			×
Adverse Cardiovascular Events		×	→	→	×
Metabolomics analysis		×			×
12-lead electrocardiogram		×	×	×	×
Blood routine examination		×	×	×	×
Liver and kidney function text		×	×	×	×
Coagulation function		×	×	×	×
Platelet aggregation rate		×	×	×	×
Blood glucose and fat		×	×	×	×
Urine and fecal routine		×	×	×	×

×, The moment of enrollment, intervention or assessments; Right arrow: indicates continued intervention or ongoing monitoring of adverse cardiovascular events. Coronary artery hemodynamic parameters, including CT-FFR and WSS; TCMSS, traditional Chinese medicine syndrome scale.

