#### Secondary outcomes

2.6.2

The secondary outcome measures of this study include imaging features of plaques, Traditional Chinese Medicine Syndrome Score (TCMSS), the Seattle Angina Questionnaire (SAQ), echocardiography, adverse cardiovascular events, and metabolomic analysis.

The imaging features of plaques include plaque morphology, location, volume, degree of stenosis, and calcification score, all of which will be assessed at baseline and 24 weeks after randomization. Echocardiography and metabolomics analyses will be performed at baseline and 24 weeks after randomization; TCMSS and SAQ will be recorded at baseline and 4th, 12th, 24th weeks after randomization. Adverse cardiovascular events are defined as cardiac death, non-fatal myocardial infarction, coronary revascularization, stroke, severe angina pectoris, and hospitalization due to acute coronary syndrome, malignant arrhythmia, or heart failure occurring within 24 weeks after randomization, and will be recorded at any time following participant enrollment.

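### Yes/no plaque features would be compared by plain chi-square or Fisher, leaving the baseline reading unused: valid overall, but inefficient and exposed to chance baseline imbalance

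*Protocol article*

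**What the plan says.** Section 2.9 (Statistical analysis), in its account of between-group comparisons, gives one line for categorical outcomes: "Categorical variables will be compared using the *χ*^2^ test or Fisher's exact test". It names no time point, no baseline term and no change category.

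Section 2.6.4 makes high-risk plaque a yes/no classification: "A plaque must exhibit two or more of the following features to be classified as a high-risk plaque". The four features are themselves present or absent. The same section defines a post-minus-pre change for CT-FFR, FAI and WSS, but none for plaque status.

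Plaque imaging is secondary: "The secondary outcome measures of this study include imaging features of plaques" (section 2.6.2). The items listed there are "all of which will be assessed at baseline and 24 weeks after randomization". Table 1 schedules "Imaging features of high-risk plaques" at day 0 and week 24, so a baseline value is planned for every participant.

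Two other parts of section 2.9 bear on the point. Imbalanced or hard-to-control confounders are to enter an analysis of covariance, and subgroup analyses are planned by presence of high-risk plaque.

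On size: "Sixty subjects will be recruited, with 30 participants allocated to each group" (section 2.7). That section calls the trial exploratory and makes no sample size calculation.

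**The concern.** Entry (section 2.2.3) requires soft or mixed plaque, not high-risk plaque, so the sample will probably mix participants with and without each feature at baseline. Those without it cannot show resolution, and those with it cannot show new occurrence. If features persist over 24 weeks, much of the variation in week-24 status only repeats baseline status. A plain two-arm test treats that variation as noise, which costs power. When the arms happen to start unequal, it also carries the inequality into the comparison.

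The covariance clause does not repair this. Analysis of covariance models a continuous outcome, and the clause acts only on an imbalance that has been observed. At stake is how much 60 participants can say about plaque features, and how far a week-24 difference can be trusted in a trial that starts unbalanced.

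**Working it through.** The protocol states no power figure, so there is none to reproduce.

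**Inputs from the protocol.** 30 per arm (section 2.7); chi-square or Fisher and a 0.05 threshold (section 2.9; two-sided assumed); a yes/no outcome read at baseline and week 24 (sections 2.6.2 and 2.6.4, Table 1).

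**Assumed, not in the documents.** Baseline prevalence *b* of 30% or 50%; the probability *s* that a feature present at baseline is still present at week 24; the probability *w* that an absent one appears; the treatment effects; no missing readings.

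**Formulas.**
- Control week-24 proportion: p = b·s + (1−b)·w.
- Correlation: phi = (s−w)·√[b(1−b)/(p(1−p))]. Example: b = 0.5, s = 0.9, w = 0.05 gives p = 0.475 and phi = 0.85·√(0.25/0.2494) = 0.85.
- Chi-square (uncorrected): z = (p₁−p₂)/√[p̄(1−p̄)(1/30+1/30)].
- Cochran-Mantel-Haenszel (CMH), over baseline strata k: z = Σ(aₖ − n₁ₖmₖ/Nₖ)/√Σ[n₁ₖn₂ₖmₖ(Nₖ−mₖ)/(Nₖ²(Nₖ−1))]. Here aₖ counts treated participants with the feature at week 24 and mₖ counts all participants with it.

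Reference value: 50% vs 25% with 30 per arm has unadjusted power of 0.52; 80% power would need 58 per arm.

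**Power (%), 20,000 simulated trials per row.** Standard error is at most √(0.25/20,000) = 0.35 points.

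| b | s/w control | s/w SYF | phi | week 24, control vs SYF | chi-square | Fisher | CMH | CMH − chi-square |
|---|---|---|---|---|---|---|---|---|
| 50 | 60/40 | 30/20 | 0.20 | 50.0 vs 25.0 | 51.5 | 40.9 | 52.3 | 0.8 |
| 50 | 80/15 | 40/10 | 0.65 | 47.5 vs 25.0 | 43.3 | 33.4 | 55.8 | 12.5 |
| 50 | 90/5 | 50/3 | 0.85 | 47.5 vs 26.5 | 38.7 | 29.4 | 65.3 | 26.6 |
| 30 | 60/40 | 30/20 | 0.18 | 46.0 vs 23.0 | 46.4 | 36.4 | 47.1 | 0.7 |
| 30 | 80/15 | 40/10 | 0.63 | 34.5 vs 19.0 | 27.6 | 19.1 | 34.0 | 6.4 |
| 30 | 90/5 | 50/3 | 0.85 | 30.5 vs 17.1 | 22.7 | 15.2 | 40.2 | 17.5 |

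The gain also depends on the effect. With control at 90/5 and SYF at 55/5, a separate simulation gives chi-square vs CMH of 15% vs 25% at 30% prevalence, 28% vs 49% at 50% and 48% vs 70% at 70%, so gains of 10 to 22 points.

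**No treatment effect: rejection rate (%).** Imbalanced means that the arms differ at baseline by at least 6 of 30 (20 points); balanced means by at most 1.

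| b | phi | overall: chi-square / Fisher / CMH | share of trials imbalanced | imbalanced: chi-square / Fisher / CMH | balanced: chi-square |
|---|---|---|---|---|---|
| 50 | 0.20 | 5.3 / 2.8 / 5.2 | 15.6 | 6.6 / 3.5 / 5.5 | 4.5 |
| 50 | 0.65 | 5.2 / 2.7 / 5.0 | 15.4 | 18.3 / 10.7 / 5.0 | 1.1 |
| 50 | 0.85 | 5.3 / 2.9 / 3.8 | 15.6 | 28.4 / 16.9 / 3.3 | 0.0 |
| 30 | 0.18 | 5.1 / 2.8 / 5.0 | 11.9 | 6.2 / 3.6 / 4.7 | 4.6 |
| 30 | 0.63 | 4.7 / 2.6 / 4.9 | 12.0 | 17.8 / 11.7 / 5.1 | 1.4 |
| 30 | 0.85 | 5.0 / 2.6 / 3.4 | 12.2 | 31.7 / 18.4 / 3.5 | 0.0 |

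Averaged over all randomizations, chi-square is nominal. Its errors are concentrated in trials that start unequal, and they almost vanish in balanced trials when phi is about 0.65 or more.

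**The case against.** The case for leaving the plan alone has real substance.

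- **Time point.** Section 2.9 does not say that week-24 status alone is tested. A chi-square on a change category (resolved, unchanged, new) would use the baseline reading. This stands as a caveat. But no such category is defined, whereas changes are defined for CT-FFR, FAI and WSS, so a comparison of week-24 status is the natural reading.
- **Subgroups.** An analysis by high-risk plaque, if it means baseline status, would compare arms within positives and within negatives. That covers part of the need. It gives no pooled baseline-adjusted test and does not reach the component features.
- **Persistence.** Nothing in the protocol says that features persist. The Discussion warns that CCTA limits may affect plaque characterization, and reading error would lower phi. This stands, and it is why the range runs down to almost no gain.
- **Rank.** Section 1 centres the hypothesis on hemodynamics and residual inflammation. Plaque stabilisation is motivation, and the plaque outcomes are secondary. Several items listed in section 2.6.2, such as volume and calcification score, are naturally continuous and outside this point.
- **Left to the SAP.** An unadjusted test is legitimate, and such detail is often settled in an analysis plan. But the article does name the test, so the remark concerns a stated choice, not an omission.

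Section 2.3 describes stratified randomization without naming the factors. Nothing says that plaque status is one; if it were, imbalance in that status would be limited.

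**Conclusion.** The point holds as a low-severity matter of efficiency and robustness. The named tests leave unused a baseline value that the trial already collects. The loss ranges from negligible when phi is near 0.2 to about 18–27 points of power at phi 0.85 for the effects tabulated, and is smaller for weaker effects. All of this rests on assumed prevalence, persistence and effects.

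A reader might infer that chi-square inflates the false-positive rate, or that baseline imbalance biases the trial. The check does not support that: the overall rate is 4.7–5.3%. The 28–32% figure applies only when phi is about 0.85, and only within the 12–16% of trials with a large chance imbalance. A reader might also infer that the protocol commits to a comparison of week-24 status alone, or that high persistence is established. The text says neither.

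**What to change.** Before unblinding, state that each yes/no plaque feature (high-risk plaque and each component) is compared between arms at week 24 with a Cochran-Mantel-Haenszel test stratified by that feature's own baseline status, in exact form if cells are sparse, whether or not imbalance is seen. Report by arm the resolution among those positive at baseline and the new occurrence among those negative. Keep chi-square or Fisher for outcomes with no baseline reading, such as adverse cardiovascular events.

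The cost is a sentence or two in section 2.9 and no new data. The downside is slight conservatism when few participants change status (null rejection of 3.4–3.8% at phi 0.85). In none of the simulated scenarios did the stratified test have less power than chi-square.

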#### Primary outcomes

2.6.1

The primary outcome measures of this study are coronary artery hemodynamic parameters and FAI assessed by CCTA. The coronary artery hemodynamic parameters include CT-FFR and WSS. These parameters will be evaluated at baseline and 24 weeks after randomization.

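### ANCOVA covariates are chosen by observed group imbalance rather than fixed in advance; adjusting the primary outcomes for their own baseline value would be more efficient than the unadjusted change-score test

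*Protocol article*

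**What the plan says.** Section 2.9 gives the between-group comparison for continuous outcomes as a t-test when the data are normal ("continuous variables with a normal distribution will be analyzed using paired" is how the sentence runs) and a rank-sum test otherwise. Neither adjusts for anything. ANCOVA follows as an addition: "difficult-to-control and intergroup imbalanced confounding factors will be analyzed as covariates using analysis of covariance to eliminate their impact on efficacy evaluation". The section names no covariate, gives no criterion for imbalance, and does not say whether the adjusted or the unadjusted result prevails. The significance rule is that a "value <0.05 will be considered statistically significant".

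Three other places bear on this:

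- Section 2.6.1 says of CT-FFR, WSS and FAI: "These parameters will be evaluated at baseline and 24 weeks after randomization". A baseline value is therefore planned for every participant.
- Section 2.6.4 turns each of these into a difference, post-treatment minus pre-treatment; for CT-FFR, "The change before and after treatment was calculated". The Abstract also describes the primary outcomes as changes.
- Section 2.3 says the sequence was generated "employing a stratified block randomization method, sequentially numbered from 1 to 60". The stratification factors are not named, and Section 2.9 does not mention strata.

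On size, Section 2.7 says "Sixty subjects will be recruited, with 30 participants allocated to each group, to investigate our research objectives" and "This study is an exploratory trial and does not require sample size calculations". It states no effect size, SD or power.

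**The concern.** Once patients are randomised, a baseline difference between groups is a chance event, not confounding. The reason to adjust is that a covariate predicts the outcome. Whether it differs between the arms in this sample is a poor guide to that. For week-24 CT-FFR, WSS or FAI, the obvious candidate predictor is the same measurement at baseline, yet under Section 2.9 it becomes a covariate only if it happens to differ between groups.

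Two things are at stake. One is efficiency: a trial of 60 with no sample size calculation has little precision to spare. The other is pre-specification: with no list and no threshold, the covariate set depends on which variables happen to differ, and two analysts following the same sentence could report different adjusted results.

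This is not a detail left to an unseen analysis plan. The article states a selection rule, and the rule is the weakness. A later plan would have to either carry it forward or contradict it.

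**Working it through.** **Inputs from the article.** 30 per arm (Section 2.7); significance level 0.05 (Section 2.9; sidedness is not stated, two-sided assumed); primary outcomes as change scores (Section 2.6.4).

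**Assumptions.** True effect d = 0.6 SD of the week-24 value; baseline to week-24 correlation r from 0.3 to 0.9; equal SD at both times. The article gives neither d nor r. It also has no power figure to reproduce. For reference, the effect detectable with 80% power in a plain two-group comparison is (1.960 + 0.842) × √(2/30) = 0.72 SD.

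**Step 1: variances, with outcome variance 1.**

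- Change score: 2(1 − r).
- ANCOVA on baseline: 1 − r².
- Ratio, ANCOVA to change score: (1 − r²) / [2(1 − r)] = (1 + r)/2.

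**Step 2: power at d = 0.6, 30 per arm.** The signal-to-noise value is d / (SD × √(2/30)). At r = 0.5:

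- Change score: SD = 1.000, so 0.6/0.2582 = 2.32, and power from the t distribution is 63%.
- ANCOVA: SD = √0.75 = 0.866, so 0.6/0.2236 = 2.68, and power is 75% (74% by simulation).

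| r | Variance, change | Variance, ANCOVA | Ratio | Power, change | Power, ANCOVA | ANCOVA n per arm matching 30 |
|---|---|---|---|---|---|---|
| 0.3 | 1.40 | 0.91 | 0.65 | 49% | 66% | 19.5 |
| 0.5 | 1.00 | 0.75 | 0.75 | 63% | 74% | 22.5 |
| 0.7 | 0.60 | 0.51 | 0.85 | 84% | 88% | 25.5 |
| 0.8 | 0.40 | 0.36 | 0.90 | 95% | 97% | 27.0 |
| 0.9 | 0.20 | 0.19 | 0.95 | 99.9% | 99.9% | 28.5 |

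Rows 0.3 to 0.7 are from 8,000 simulated trials each and agree with the t-based formula to about 1 point. Rows 0.8 and 0.9 are from the formula. The last column is 30 × (1 + r)/2.

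Power near 100% hides the difference at high r. If the effect is instead set so that the change score has exactly 80% power, ANCOVA has 93.5%, 89.9%, 86.0%, 84.0% and 82.0% at r = 0.3, 0.5, 0.7, 0.8 and 0.9.

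**Step 3: what an imbalance rule recovers.** Section 2.9 gives no trigger, so one has to be supplied: adjust for baseline only if its between-group p-value is below 0.05, otherwise use the change score. Simulated power at d = 0.6 is then 50%, 64% and 84% at r = 0.3, 0.5 and 0.7, almost the same as the unadjusted change score. A second simulation used d = 0.5, six candidate covariates (baseline, plus five others explaining 15% of outcome variance) and 5,000 runs per setting. At r = 0.5 and 0.7 it gave:

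- Imbalance-selected: 45.0% and 69.5%.
- Unadjusted change score: 45.6% and 68.8%.
- ANCOVA fixed on baseline: 57.3% and 75.7%.

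**Step 4: type I error, same six-covariate simulation.** Mechanical imbalance selection on change scores gave 4.2% (r = 0.5) and 3.9% (r = 0.7). Taking the smallest p-value among the unadjusted test and six single-covariate ANCOVAs gave 10.2% and 10.6%. The chance of at least one imbalance at p < 0.05 is 1 − 0.95⁶ = 26% with six independent candidates and 1 − 0.95¹⁰ = 40% with ten.

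**Step 5: strata left out.** In a simulation with two balanced strata explaining 10% to 30% of outcome variance, an analysis ignoring them had type I error of 3.7% down to 2.0%. The test becomes conservative.

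**The case against.** The strongest reply is that baseline is not ignored. Sections 2.6.4 and the Abstract make the primary outcomes changes from baseline, so it enters every primary comparison. That stands, and it limits the point to relative efficiency. A reader might infer from Section 2.9 that baseline is discarded; the article does not support that.

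The size is conditional: d and r are both assumed, the 17-point gap belongs to the lowest r shown, and above r = 0.8 little is left. That stands too. The p < 0.05 trigger in Step 3 is likewise a construction; the article fixes none, and its wording reads as ANCOVA supplementing the main test, not replacing it.

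A reader might also infer that choosing covariates by imbalance raises the false-positive rate. Applied mechanically it does not. The rise to about 10% needs the result to be picked from several adjusted analyses, a practice the article does not describe. Section 2.4 keeps the statistician on coded groups until the primary analysis is done, which prevents knowingly favouring the active arm, though imbalances and p-values remain visible under the codes. Imbalance could also be judged before outcome data are examined; Section 2.9 gives no timing.

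On strata, the article does not name the factors, and a condensed article may leave them to the full protocol. A reader might infer a false-positive risk from omitting them; the effect runs the other way.

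Finally, Section 2.7 calls the trial exploratory, so there is no power target to miss. This lessens the concern but does not remove it: Section 2.1 also calls it a superiority trial, and Section 2.9 tests at 0.05.

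**Conclusion.** The concern holds as a matter of efficiency and pre-specification. Section 2.9 ties adjustment to observed imbalance, which is the wrong criterion in a randomised trial, and leaves the covariate set unfixed. For the primary outcomes, the change score gives away precision that baseline-adjusted ANCOVA would keep. The gain is worth having at r = 0.3 to 0.5 (17 and 11 points at d = 0.6), modest at 0.7 (4 points) and small at 0.8 to 0.9 (about 2 to 4 points where the change score has 80% power). These figures assume equal SDs, two-sided testing and complete data on 30 per arm. The variance ratio (1 + r)/2 does not depend on d, and ANCOVA comes out no worse at any r in the range, apart from the degree of freedom it uses. No inflation of type I error follows from the rule as written, and leaving out the strata costs precision without adding false positives. The point merits a change to the plan but does not by itself undermine the trial's validity.

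**What to change.** In Section 2.9, make the primary analysis of each continuous primary outcome an ANCOVA of the week-24 value (or the change) on treatment, the baseline value of that outcome and the stratification factor(s) used in randomisation, all fixed before unblinding. Name those factors or cite the full protocol for them. Delete selection by imbalance, or keep it as a labelled sensitivity analysis with its covariates listed in advance. State that the primary ANCOVA result prevails if analyses differ.

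The cost is wording and a few degrees of freedom: an unadjusted comparison of 60 has 58, the baseline value takes one, and the strata take a number the article does not allow one to count. No new data are needed. Section 2.2.1 expects completion in the first quarter of 2026; if unblinding has already occurred, the revised analysis should be reported as post hoc.
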